## Abstract

**Background:**

Acute renal colic caused by urinary calculi (ARCUC) has a considerable impact on the quality of life. Acupuncture might be a potential treatment option. However, the evidence is limited. We will conduct this trial to evaluate the efficacy and safety of acupuncture as adjunctive treatment to diclofenac for ARCUC.

**Methods/design:**

A total of 80 eligible patients who are diagnosed with urinary stone renal colic will be randomly allocated to the acupuncture group or the sham acupuncture group. Each patient will receive 1 session of acupuncture or sham acupuncture. The primary outcome will be the response rate of patients achieving a reduction of > 50% on visual analog score (VAS) from baseline to 10 min after treatment. Secondary outcomes will include the VAS, remedial analgesia, re-visit and admission rate, blinding assessment, credibility and expectancy, and adverse event. All patients who receive randomization will be included in the intent-to-treat analysis.

**Discussion:**

The finding of this trial will provide evidence on the efficacy and safety of acupuncture for the treatment of ARCUC. The results of this study will be published in peer-reviewed journals.

**Trial registration:**

ClinicalTrials.gov ChiCTR 1900025202. Registered on August 16, 2019.

**Supplementary Information:**

The online version contains supplementary material available at 10.1186/s13063-021-05600-2.

## Background

Acute renal colic caused by urinary calculi (ARCUC) is described as acute unbearable paroxysmal pain in the lower back or upper abdomen, with or without hematuria, nausea, and vomiting [1]. The urinary stone disease was increasingly prevalent, with a lifetime risk of about 12% in men and 6% in women [2]. The prevalence of kidney stones in China was 6.4% (6.5% in men and 5.1% in women) [3]. In the USA, more than one million patients visit the emergency department for the ARCUC every year [4]. It is described as one of the worst pains a patient could have and has a considerable impact on quality of life.

Pain relief is the primary goal in the management of patients with ARCUC [1]. NSAIDs offer effective sustained analgesia for ARCUC in the emergency department [5] and result in a lower need for rescue analgesia [6]. The 2017 update of the European Association of Urology (EAU) guidelines recommends NSAIDs as the first-line analgesic [1]. However, its clinical application is partly limited to the increased risk of major coronary events which increase with dose and duration [7, 8]. Furthermore, the onset time of NSAIDs is relatively slow, with the time to peak plasma concentration of 10–30 min after intramuscular injection [9]. More than 30% of patients did not achieve satisfactory relief of pain after had NSAIDs [5]. Adjunctive therapy with a quick analgesia effect and less adverse events is needed for patients with ARCUC.

Acupuncture is a complementary therapy from traditional Chinese medicine, which has the advantages of quick analgesia [10, 11]. A meta-analysis suggested that acupuncture may be a potential therapy for ARCUC [12]. However, to our knowledge, there is no randomized controlled trial (RCT) to measure the efficacy of acupuncture as an adjunctive treatment to NSAIDs for ARCUC. This randomized, participant-blind, sham-controlled trial is designed to evaluate the efficacy and safety of acupuncture as an adjunctive treatment to diclofenac for ARCUC.

## Methods/design

### Study design

This study is a single-center, randomized, participant-blind, sham-controlled trial. Each participant will receive one session of acupuncture or sham acupuncture and be followed up for 1 week after treatment. The current protocol (version v1.0, 2019.4.21) has been approved by the ethics committee of Beijing Hospital of Traditional Chinese Medicine Affiliated to Capital Medical University (ER.03.03-V1.04) and registered with the Chinese Clinical Trial Registry (ChiCTR 1900025202; registration date: 16 August 2019) before recruiting the first participant. Figure 1 shows the flow diagram of the study. The study is guided by the Declaration of Helsinki and the Standard Protocol Items: Recommendations for Interventional Trials (SPIRIT) (Additional file 1) [13].

**Fig. 1 Fig1:**
[figure not shown]
Flow diagram

### Patient recruitment

Participants who are diagnosed as ARCUC according to the guideline of the European Association of Urology will be recruited at Beijing Hospital of Traditional Chinese Medicine Affiliated to Capital Medical University [1]. The recruitment strategy will primarily contain advertisements on hospital social Internet media (WeChat), outpatient clinics, and the emergency room. Written informed consent will be provided by each patient through a research assistant before randomization.

### Inclusion criteria

Diagnosed as ARCUC according to the guideline of the European Association of Urology (2017) [1]Aged 18–75 years (either sex)Pain intensity of 4 or more out of 10 on a visual analog scale (VAS) [14]Written informed consent

### Exclusion criteria

Use of any analgesia in the last 6 hAllergic to diclofenac sodium, morphine, or anisodamine; history of asthma, urticaria, or allergic rhinitis ascribed to acetylsalicylic acid or other drugs containing prostaglandin synthase inhibitorsCongestive heart failure, acute ischemic heart disease, or peripheral vascular disease; acute cerebrovascular disease, increased intracranial pressure; renal or liver failureActive digestive ulcer, pyloric obstruction, or intestinal obstructionBlood system diseases such as hemophilia, coagulation disorders in patients; thrombocytopenia (< 50× 10^9^/L); using anticoagulantsGlaucoma, elevated intraocular pressureSerious adverse reactions to acupuncture; skin infection at the acupuncture siteHistory of mental illness or substance abuse or have severe cognitive impairmentPregnant or lactating

### Randomization, allocation concealment, and masking

Eighty eligible patients will be randomly assigned to the acupuncture group or the sham acupuncture group in a 1:1 ratio. The blocked randomization sequence will be computer-generated with the SAS 9.4 software by an independent professional statistician ([name], Beijing Hospital of Traditional Chinese Medicine, Capital Medical University), who is not involved in the implementation and statistical analysis of the trial. The sealed envelopes will be numbered in sequential order from 1 to 80 to hide the group assignments and be saved by a research assistant who does not take part in enrolling patients. When eligible patients are enrolled in the trial, envelopes will be successively opened by the clinical research coordinators who are responsible for enrolling the patients. Due to the responsibility of providing acupuncture and sham acupuncture, the acupuncturists will not be masked. Patients in the two acupuncture groups will be treated in a single treatment room and be blinded to which acupuncture method they would receive. In addition, outcome assessors and statisticians who perform the statistical analyses will be blinded. The group assignments will be revealed after the statistical analysis is completed.

### Interventions

Patients in both the acupuncture group and sham acupuncture group will receive 50 mg/2 mL diclofenac sodium intramuscular injection after randomization (Guangdong Bangmin Pharmaceutical Co., Ltd.). Both acupuncture and sham acupuncture will be performed by the licensed doctors of traditional Chinese medicine with at least 5 years of experience. Meanwhile, acupuncture will be performed by the licensed doctors of traditional Chinese medicine who have been trained how to locate acupoints and non-acupoints, puncture, and manipulate needles before the trial. Sterile disposable stainless steel acupuncture needles (a length of 40 mm, a diameter of 0.3 mm; Hwato, Suzhou, China) will be used. Both acupuncture and sham acupuncture treatment will only consist of 1 session treatment with 30 min. Needles will be removed if the patients suffer from any adverse events (AEs). Patients will receive 0.1 mg/kg intravenous morphine (Northeast Pharmaceutical Group Shenyang First Pharmaceutical Co., Ltd.) and 10 mg intramuscular racanisodamine (Tianjin KingYork Pharmaceutical Co., Ltd.) if they report the severity of pain more than 8 points on the VAS after puncturing the needles. No additional intravenous fluid will be administered in the first 60 min after administration of the diclofenac sodium.

### Acupuncture

Patients allocated to the acupuncture group will be punctured at the pre-specified acupoints. According to the theory of traditional Chinese medicine and clinical experience, bilateral Yaotongdian (EX-UE 7) will be used. According to the National standard of the People’s Republic of China, EX-UE 7 will contain two points on the dorsum of the hand. The one is between the second and the third metacarpal bones, and the other is between the fourth and the fifth metacarpal bones. These two points are of the same distance to the metacarpophalangeal joints and the transverse crease of the wrist. The localization of EX-UE 7 is exhibited in Fig. 2. Four needles will be used per patient, and the depth of needle insertion will be 10–15 mm. Manipulations of twirling, lifting, and thrusting will be performed on all needles for at least 30s to reach De qi (a compositional sensation including soreness, numbness, distention, and heaviness), which is believed to be an essential component for acupuncture efficacy.

**Fig. 2 Fig2:**
[figure not shown]
Locations of acupoints and non-acupoints. Red points are the acupoints used in the acupuncture group; green points are the non-acupoints used in the sham acupuncture group. The 16 non-acupoints will be randomly assigned to 8 subgroups. The patients in the sham acupuncture group will be assigned into 1 of these 8 subgroups, and the 2 non-acupoints in this subgroup will be used on this patient in the whole treatment period. NA, non-acupoint

### Sham acupuncture

A superficial skin penetration (1–4 mm in depth) at non-acupoints will be performed in the sham acupuncture group, without needle manipulation for De qi. Based on the search and analyses of traditional Chinese medicine reference books and acupuncture modern articles, the acupoints with effects on alleviating ARCUC or pain have been screened. After excluding these acupoints, 16 points without effects on ARCUC and pain are extracted and the locations 3 mm apart from these 16 acupoints are defined as non-acupoints, which are used in the sham acupuncture group. The locations of these non-acupoints are shown in Table 1 and Fig. 2. To make the quantity of stimulus uniform between two groups, the same number of needles for sham acupuncture will be the same as those in verum acupuncture. The 16 non-acupoints will be randomly assigned to 8 subgroups and will be recorded in predetermined computer-made randomization sealed envelopes. Each subgroup has bilateral 2 non-acupoints on the arms. The patients in the sham acupuncture group will be assigned into 1 of these 8 subgroups. This method to define non-acupoints in sham acupuncture has been used in previous acupuncture trials [15, 16].

**Table 1 Tab1:** Locations of non-acupoints in the sham acupuncture group

Subgroup	Non-acupoints	Locations
1	NA 1	3 mm lateral to the Shanglian (LI9) horizontally
	NA 3	3 mm lateral to the Pianli (LI6) horizontally
2	NA 4	3 mm lateral to the Sidu (TE9) horizontally
	NA 16	3 mm lateral to the Yinxi (HT6) horizontally
3	NA 6	3 mm lateral to the Zhigou (TE6) horizontally
	NA 8	3 mm lateral to the Kongzui (LU6) horizontally
4	NA 12	3 mm lateral to the Jianshi (PC5) horizontally
	NA 2	3 mm lateral to the Xialian (LI8) horizontally
5	NA 7	3 mm lateral to the Zhizheng (SI7) horizontally
	NA 11	3 mm lateral to the Erbai (EX-UE2) horizontally
6	NA 5	3 mm lateral to the Sanyangluo (TE8) horizontally
	NA 13	3 mm lateral to the Jingqu (LU8) horizontally
7	NA 9	3 mm lateral to the Ximen (PC4) horizontally
	NA 15	3 mm lateral to the Tongli (HT5) horizontally
8	NA 14	3 mm lateral to the Lingdao (HT4) horizontally
	NA 10	3 mm internal to the Erbai (EX-UE2) horizontally

*NA* non-acupoint

### Outcomes

#### Primary outcome

The primary outcome will be the response rate after 10 min of puncturing of the needles, which is defined as the proportion of participants whose pain score on VAS reduces at least 50% compared with baseline [5].

#### Secondary outcomes

##### Total pain

The total pain will be defined by the area under the curve during the 60 min after puncturing the needles [17]. The pain will be assessed using a VAS [14] with scores ranging from 0 to 10 after 0, 1, 5, 10, 15, 20, 30, 45, and 60 min of puncturing of the needles. The bigger area under the curve indicates worse pain.

##### Response rate at other times

The proportion of participants achieving significant pain reduction will also be measured after 1, 5, 15, 20, 30, 45, and 60 min of the puncturing the needles.

##### Remedial analgesia

The number of patients who receive intravenous morphine and intramuscular racanisodamine will be recorded after 60 min of the puncturing the needles.

##### Re-visit and admission rate

The numbers of patients who re-visit the emergency department or are hospitalized will be evaluated during 72 h after puncturing the needles.

##### Blinding assessment

All patients will be asked to guess whether they receive acupuncture or sham acupuncture after acupuncture treatment to measure the patient-blinding effects.

##### Credibility and expectancy

The credibility and expectancy of patients will be assessed using the Credibility/Expectancy Questionnaire [18] after removing the needles. Items will be converted to *Z* scores before averaging, and the scale has a mean of 0.0 (SD, 1.0). The *Z* score is negative when the credibility/expectancy is below the mean and positive when it is above the mean.

##### Adverse events

All adverse events will be recorded by outcome assessors during 7 days after treatment. Based on the potential relationship between needling and adverse events, adverse events will be categorized as treatment-related or not.

The schedule of enrolment, intervention, and assessments is shown in Fig. 3.

**Fig. 3 Fig3:**
[figure not shown]
Schedule of enrollment, intervention, and assessments of this study protocol. Min, minutes

#### Quality control

Both paper files and electronic documents will be preserved for at least 5 years after publication. If readers have any questions, they can contact the corresponding author for access to the original data. Patient information will remain anonymous, including name, ID number, and telephone number. The protocol will be reviewed and revised by experts in acupuncture, emergency, urinary surgery, methodology, and statistics. We will perform a pre-specified standard operating procedure, which includes screening patients, improve relevant inspection, intramuscular injection of diclofenac, acupuncture, filling out the CRF, assessing outcomes, and data management. On-site monitoring will be adopted in this trial per 3 months. The ethics committee of Beijing Hospital of Traditional Chinese Medicine Affiliated to Capital Medical University will audit trial conduct per 12 months.

#### Sample size

In this study, the sample size was priori calculated. Based on the previous literature [19] and our clinical experience, the response rates in the acupuncture group and sham acupuncture group are expected to be 70% and 40%, respectively. The ratio between acupuncture group and sham acupuncture group was 1:1. A sample size of 80 patients (40 in each group) is estimated to have at least 80% power to detect difference between groups at a 2-sided significance level of 5% according to the formula: $$ n={\left[\frac{{\mathrm{z}}_{\alpha}\;\sqrt{4{\pi}_c\;\left(1-{\pi}_c\right)}+{\mathrm{z}}_{\beta}\;\sqrt{2{\pi}_1\;\left(1-{\pi}_1\right)+{\pi}_2\;\left(1-{\pi}_2\right)}}{\pi_1-{\pi}_2}\right]}^2 $$. Because there is only one session of acupuncture treatment and almost no shedding, no loss to follow-up is considered. Thus, the recruitment goal was set at 80 patients.

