### Statistical analysis

Patients’ baseline characteristics will be summarized based on groups. Continuous variables will be described using the mean (standard deviation), or the median (interquartile range) if the normality assumption is violated. Student’s *t* test or Wilcoxon rank sum test (if normality is violated) will be used for comparison of continuous variables among the two groups. Categorical variables will be described using the frequency (percentage) and compared using the chi-squared test.

For the primary comparison, the chi-squared test will be used for the response rate (the proportion of participants whose pain reduced ≥ 50% compared with baseline). For the secondary outcomes, Student’s *t* test, chi-squared test, Fisher’s exact test or the Wilcoxon rank sum test will be used to test the difference of the outcomes including the total pain, remedial analgesia, re-visit and admission rate, blinding assessment, credibility and expectancy, and adverse events, between groups according to the distribution of variables. There is no interim analysis or additional analysis in this trial.

All efficacy analyses will be performed using the intention-to-treat set, which includes all randomized patients. Missing data will be dealt with the last observation carried forward (LOCF). All analyses will be performed using SPSS version 23.0 (IBM SPSS Statistics, NY, USA). The level of significance will be established at *α* < 0.05 with a two-sided test.

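### The sample-size formula is misprinted and, once corrected, gives 84 patients rather than 80; power at 80 is about 78% by that formula (79.6% exact), a small shortfall from the stated minimum of 80%

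*Protocol article*

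**What the plan says.** All the design inputs stand in the protocol article, section Sample size:

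- Response rates: "the response rates in the acupuncture group and sham acupuncture group are expected to be 70% and 40%, respectively".
- Allocation: "The ratio between acupuncture group and sham acupuncture group was 1:1".
- Size and power: "A sample size of 80 patients (40 in each group) is estimated to have at least 80% power to detect difference between groups".
- Error rate and method: "at a 2-sided significance level of 5% according to the formula", followed by the formula itself.
- Losses: "no loss to follow-up is considered. Thus, the recruitment goal was set at 80 patients".

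The expression under the second square root of the formula is typeset as "2{\pi}_1\;\left(1-{\pi}_1\right)+{\pi}_2\;\left(1-{\pi}_2" and then closes. In ordinary notation this is 2π₁(1−π₁) + π₂(1−π₂), with no bracket around the sum. The first root is 4πc(1−πc).

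The Statistical analysis section fixes the test that the power should refer to: "For the primary comparison, the chi-squared test will be used for the response rate".

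**The concern.** The article makes its power a consequence of a formula it prints, so a reader can check one against the other. The two roots do not match. The first is the null-variance term for a total sample size split equally between two arms. The second gives one arm's variance twice the weight of the other's, which no derivation with 1:1 allocation produces.

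The slip matters because the stated size falls between the two results. The printed version gives a number below 80 and the corrected version a number above it. The claim that 80 patients reach a power of 80% or more is thus supported by the formula only while the formula is wrong. At stake is a headline design figure that will be carried into the report of results. No analysis or estimate depends on it.

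**Working it through.** **Inputs.** π₁ = 0.70 and π₂ = 0.40, so the difference is 0.30; 1:1 allocation; two-sided 5%; 80% power; no losses. All are from the Sample size section. The article does not define πc. I take it as the mean rate, (0.70 + 0.40)/2 = 0.55. The normal quantiles are 1.95996 (two-sided 5%) and 0.84162 (80% power).

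**What the formula should be.** Let n be the total, with n/2 per arm.

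- Under the null, the variance of the difference is πc(1−πc)(2/n + 2/n) = 4πc(1−πc)/n. This matches the first printed root, so n is the total.
- Under the alternative, the variance is π₁(1−π₁)(2/n) + π₂(1−π₂)(2/n) = 2[π₁(1−π₁) + π₂(1−π₂)]/n. The second root must therefore contain 2[π₁(1−π₁) + π₂(1−π₂)].

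**Values under the roots.**

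- First root: 4 × 0.55 × 0.45 = 0.99
- Second root as printed: 2 × 0.21 + 0.24 = 0.66
- Second root corrected: 2 × (0.21 + 0.24) = 0.90

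**Sample size by the formula as printed.** [(1.95996 × √0.99 + 0.84162 × √0.66)/0.30]² = 77.08, so 78 patients (39 per arm). Exchanging the labels of the two arms changes the second root to 2 × 0.24 + 0.21 = 0.69 and the result to 77.98. A two-sided formula for equal arms should not depend on the labelling, which confirms that the expression is a misprint.

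**Sample size by the corrected formula.** [(1.95996 × √0.99 + 0.84162 × √0.90)/0.30]² = 83.94, so 84 patients (42 per arm).

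**Sample size by the unpooled formula (not the one printed).** (1.95996 + 0.84162)² × (0.21 + 0.24)/0.30² = 39.24 per arm, so 40 per arm and 80 in total. Of these three calculations, this is the only one that reproduces the stated 80 directly.

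**Power at 40 per arm.**

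| Method | Power |
|---|---|
| Corrected (pooled) formula: Φ[(0.30 × √80 − 1.95996 × √0.99)/√0.90] = Φ(0.773) | 78.0% |
| Exact, chi-squared without continuity correction | 79.6% |
| Unpooled normal approximation: Φ[0.30/√(0.45/40) − 1.95996] = Φ(0.868) | 80.7% |

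The exact figure adds the binomial probabilities of every pair of responder counts (40 patients at 0.70, 40 at 0.40) whose Pearson statistic is at least 3.841. The same enumeration gives 81.3% at 41 per arm.

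**The case against.** The strongest reply is that 80 is a defensible number. The unpooled formula is a standard one. With the article's own inputs it gives exactly 40 per arm and a nominal power of 80.7%. The printed formula taken literally gives 78, not 80, so the missing bracket may be a typesetting slip that played no part in the calculation. The exact power of the uncorrected chi-squared test is only 0.4 points below 80%, and one more patient per arm would pass it. The 70% and 40% are round expectations from earlier literature and clinical experience, and a gap of this size lies well inside their uncertainty.

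Most of this stands, and it rules out several stronger readings that a reader might infer:

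- *That 80 patients meet the claim only under the wrong formula, or that the misprint produced the 80.* The unpooled result contradicts the first, and the article does not show its calculation, so the second cannot be established.
- *That power falls to 72.5%.* This is the exact figure at 40 per arm with a continuity correction or Fisher's exact test. The Statistical analysis section names the chi-squared test for the primary comparison and mentions Fisher's test only for secondary outcomes. Whether a continuity correction applies is a detail commonly left to the analysis plan, which is not shown.
- *That a few lost patients would erode the power further.* All randomized patients are to be analysed, with missing values carried forward, and the primary outcome is read 10 minutes after needling. Losses would not simply shrink the denominator.

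What the reply does not remove is the mismatch in the text. The article cites a pooled formula, not the unpooled one, and the corrected pooled formula does not give 80. Nor does the unpooled figure secure a lower bound of 80% for the planned test, whose exact power without correction is 79.6%.

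**Conclusion.** The formula is wrong as printed, and the statement that 80 patients give a power of 80% or more does not follow from it once it is corrected. The corrected formula needs 84 patients, 4 more than planned (5%). At 80 patients the shortfall is 2.0 points by that formula (80 − 78.0) and 0.4 points by exact enumeration (80 − 79.6). This rests on the article's 70% and 40%, on πc being the mean of the two rates, and on a chi-squared test without continuity correction. It is a small correction to a stated design figure. It is not evidence that the trial is materially underpowered.

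**What to change.** In the Sample size section:

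1. Restore the bracket, so that the second root reads √(2[π₁(1−π₁) + π₂(1−π₂)]). If another formula produced the 80, name and print that one instead.
2. Replace the claim of a minimum of 80% with: about 78% by the corrected formula (79.6% exact, uncorrected Pearson chi-squared). If the unpooled formula turns out to be the source, its nominal 80.7% can be given, with the exact 79.6% beside it.

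The recruitment goal of 80 can stay. The only cost is a slightly less favourable stated power.
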